## Results

This study was recently initiated at the *Laboratoire de pathokinésiologie* of the Centre de recherche interdisciplinaire en réadaptation du Montréal métropolitain (CRIR), Québec, Canada, which is part of the Centre intégré universitaire de santé et de services sociaux du Centre-Sud-de-l’Ile-de-Montréal in Montreal, Canada, and at the *Laboratoire du muscle et de sa fonction* of the Université du Québec à Montréal. This project received ethical approval on March 14, 2019, from the CRIR ethics committee and was registered on June 7, 2019, with the US National Library of Medicine at ClinicalTrials.gov (NCT03989752). This study is expected to be completed by spring 2021, with results to follow shortly after.

## Discussion

### Overview

This project innovates by being among the first studies to comprehensively, prospectively, and longitudinally investigate the effects of a wearable robotic exoskeleton–assisted walking program among long-term WU_SCI_ who have a very poor prognosis for walking recovery [101]. This study investigates the effects on organic systems, functional capacities, and multifaceted psychosocial factors. This study also investigates the influence of walking program attributes (eg, duration, training frequency, and intensity) on these effects. This project is crucial in strengthening evidence in this field based on hierarchical forms of knowledge creation. This project is also timely, since WU_SCI_ are now requesting the democratization of accessibility to this technology during rehabilitation and in the community at a faster rate than evidence is generated and shared with physical activity and rehabilitation professionals, administrators, and policy makers. Strengthened evidence is urgently needed to fill this knowledge gap to some extent and to start informing the decision-making process of these stakeholders regarding the possibility of purchasing wearable robotic exoskeletons as well as developing, implementing, and evaluating activity-based and adapted physical activity programs with wearable robotic exoskeletons in clinical practice (eg, walking program). Moreover, this evidence, once coupled with clients’ perspectives, may become key precursors to (1) develop and implement community- and/or home-based walking programs, (2) advocate for policy changes to broaden accessibility to wearable robotic exoskeletons, and (3) propel future larger-scale pragmatic or randomized controlled trials with an appropriate comparator targeting the effectiveness of walking programs with a wearable robotic exoskeleton. Of even greater relevance, it is expected that walking programs with a wearable robotic exoskeleton will reduce impairments (ie, organic systems) and optimize aptitudes, which are expected to positively influence psychosocial outcomes in WU_SCI_ and potentially those with other sensorimotor impairments (eg, stroke). In the long term, although not measured in the proposed study, we can hypothesize that indirect societal benefits may become tangible via reduced caregiver burden and reduced health care costs, for example. By optimizing their global health, especially as they age, WU_SCI_ will also remain in a *state of readiness* to benefit from future advances in neural repair, recovery, or rehabilitation technology. Lastly, as some wearable robotic exoskeletons may become approved for home or community use by Health Canada, some WU_SCI_ are now envisioning their use as personal neuroprostheses for ambulation in their daily lives as a complement to wheelchair mobility in the near future. Still, strengthened evidence is needed to support the prescription and reimbursement processes in order to accelerate uptake of wearable robotic exoskeletons in the community.

Many stakeholders may benefit from this interventional study. For WU_SCI_ who have no or very limited walking ability, the walking program with the wearable robotic exoskeleton is not expected to have any reversal effect on their walking capacity without this novel mobility assistive technology. However, this project is relevant since it will generate the first evidence of the anticipated cardiorespiratory, musculoskeletal, and endocrine-metabolic health adaptations upon completion of a walking program with a wearable robotic exoskeleton. For the first time, the extent to which these adaptations translate into beneficial effects on functional capacity will also be verified, as will their effects on health-related quality of life and psychological health. This includes the psychological well-being domain, which was not specifically measured during the feasibility study but was mentioned by the majority of participants. Given the fact that the population of WU_SCI_ continues to grow and that they now live longer, these potential beneficial effects are further warranted. The caregiver burden and the potentially costly long-term expenditures associated with adverse health events may also decrease. For rehabilitation professionals, the proposed project is relevant since strengthened evidence regarding the effects of the walking program and the characteristics of the best responders will be generated and will inform clinical decision-making processes or the development of a clinical algorithm for referring individuals with SCIs to a walking program. For rehabilitation program administrators and policy makers, the proposed study is relevant since the evidence generated may further confirm the need for publicly funded clinical and technological infrastructures to create structured programs incorporating walking technologies, such as the wearable robotic exoskeleton, and outcome measures into rehabilitation or adapted physical activity centers. Both program administrators and policy makers will need to work collaboratively and cohesively to develop creative solutions to address this current service gap and engage in transformative improvements. For the research community, this project provides a unique opportunity to create a strong multidisciplinary team of well-established scientists with diverse and complementary academic training as well as clinical and fundamental research expertise. For manufacturers with an interest in wearable robotic exoskeletons, among others, this project is relevant since the input from powered exoskeleton end users (ie, WU_SCI_) will become available and may enrich the continuous quality improvement process. This process is imperative to further support and accelerate the development of wearable robotic exoskeletons and to reach key commercialization milestones for the technology to become personalized and accessible for WU_SCI_ interested in home or community use (ie, neuroprosthesis) in the next decade.

### Potential Challenges and Appropriate Mitigation Strategies

A few potential challenges merit attention:

Some potential participants will have insufficient passive range of motion at the lower extremities to engage with the project. These participants will be provided with a 4- to 6-week home-based stretching program, will be reassessed, and may become eligible later.Female WU_SCI_ may be underrepresented. Efforts will be made for the sample to be representative of the SCI population and to have women make up 20% of the sample. However, since the minority of individuals affected by SCIs are female and the sample size is limited (n=20), it is unlikely that statistical analysis by subgroups (ie, male vs female) will be feasible in order to account for potential sex and gender differences. Nonetheless, descriptive statistics will present results separately for women and men whenever indicated.A small number of participants may demonstrate vitamin D deficiencies [102]. To mitigate this risk, at T_0_, the equivalent of 1 year of vitamin D3 supplementation will be provided to all participants who are not currently taking supplements. Moreover, all participants will be instructed on healthy balanced diets.Some participants may concurrently engage in extraneous physical activity or may seek cointerventions during the project. Participants will be asked to maintain their customary level of physical activity during the project and to avoid engaging in new cointerventions. Any unintended intervention (ie, contamination or cointervention) that may influence the results will be documented and its effect carefully verified by the research team and possibly considered as a dichotomous variable (ie, present vs absent).Some participants may experience some lower extremity neurorecovery. In the event a participant was to experience neurorecovery (ie, lower extremity motor score of ≥20 on the American Spinal Injury Association Impairment Scale), he or she would be withdrawn from the project and referred for a comprehensive neurological assessment and to an advanced locomotor training program.

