## Methods

### Study Design

A prospective, longitudinal, self-controlled interventional study with multiple discrete measurement times will be used to assess outcomes at baseline (ie, preintervention phase), during the intervention, and thereafter (ie, retention phases) (see Figure 2). While this design may contrast with *classic* study designs frequently recommending a separate comparison group to assess efficacy or effectiveness, the use of a separate comparison group was judged as nonideal in the context of this study, based on the challenges linked to the classification and quantification of the severity of SCIs and their heterogeneous consequences [65]. In addition, interventional trials of new technologies document that potential participants are reluctant to participate, refuse to adhere to the requirements of a control group, or withdraw for the most part from a control group [66,67]. To strike an optimal balance between the need to have a control group with the anticipated strong desire of potential participants to engage in the wearable robotic exoskeleton–assisted walking program, while also considering the amount of, and timeline limits linked to, the study’s funding, the study includes a 4-week observation phase prior to the start of the intervention. Since only individuals with a chronic SCI with *stable* overall health status and life habits will be recruited, outcome measures will be assessed at the start and at the end of the 4-week observation phase. These outcome measures will provide data about each participant’s natural variability and will enable us to detect whether the intervention has an effect greater than the underlying natural variability (ie, patient-specific minimal detectable change criteria computed); they will also enable us to test the effects of the intervention (ie, pre- vs postintervention responses). This boosts the ethical acceptability of the project, minimizes the impacts of potential and unmeasured confounding variables, facilitates recruitment, and mitigates the risk of experimental attrition. Lastly, semistructured interviews and an online questionnaire will capture participants’ satisfaction levels and perspectives about the wearable robotic exoskeleton–assisted walking program and the mobility technology in itself (ie, the wearable robotic exoskeleton).

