### Intervention: Overground Wearable Robotic Exoskeleton–Assisted Walking Program

An Ekso GT (Ekso Bionics) wearable robotic exoskeleton, which has been approved by Health Canada, is used in this study (see Figure 1). At T_1_, participants engage in a wearable robotic exoskeleton–assisted overground walking program that encompasses 34 training sessions offered over a 16-week period. The number of training sessions per week progressively increases to safely and efficiently adhere to the overload principle (see Figure 3). The duration of the training program mimics that of a recent study that confirms for the first time an improvement in bone turnover among individuals with a chronic SCI following a 16-week walking program [39]. The frequency of the training program that progresses from one to three sessions per week matches the latest recommendation from the Physical Activity Guidelines for Adults with SCI, including the new conditional recommendation to engage in at least 30 minutes of moderate-to-vigorous intensity aerobic exercise three times per week for cardiometabolic health benefits [68]. All training sessions are supervised by a certified physiotherapist as well as a physiotherapy assistant as needed [46,53]. During each 60-minute training session, participants perform sit-stand transfers and walk with the wearable robotic exoskeleton and a walking aid (ie, rolling walker or forearm crutches). Verbal and tactile feedback are provided by the physiotherapist as needed.

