	**Blood biomarkers**					
		Bone turnover (serum procollagen type 1 N-terminal peptide, osteocalcin, C-terminal cross-linking telopeptide, and 25-hydroxyvitamin D)	✓	✓	✓	✓
		Glycemia (fasting glucose, insulin, and glycosylated hemoglobin)	✓	✓	✓	✓
		Insulin resistance (homeostatic model assessment)	✓	✓	✓	✓
		Lipids (total cholesterol, high-density lipoprotein, low-density lipoprotein, triglycerides, and apolipoprotein B)	✓	✓	✓	✓
		Inflammation (C-reactive protein, tumor necrosis factor alpha, interleuken-6, and interleuken-10)	✓	✓	✓	✓

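### Vitamin D3 is newly supplied at T0, yet T0–T1 is read as natural variability, T1–T2 change is credited to walking, and 25-hydroxyvitamin D is itself an outcome

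*Protocol article*

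**What the plan says.** All places are in the protocol article.

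- **Supplement and diet (Potential Challenges and Appropriate Mitigation Strategies).** The stated reason is that "A small number of participants may demonstrate vitamin D deficiencies". The measure is that "at T_0_, the equivalent of 1 year of vitamin D3 supplementation will be provided to all participants who are not currently taking supplements". In addition, "all participants will be instructed on healthy balanced diets"; no time is given for this.
- **Control phase (Study Design).** In place of a comparison group, "the study includes a 4-week observation phase prior to the start of the intervention". It is justified by the claim that only people with stable "overall health status and life habits will be recruited". The measurements at its two ends "will enable us to detect whether the intervention has an effect greater than the underlying natural variability", through a minimal detectable change computed for each participant. The pre-post comparison then tests the intervention.
- **Intervention (Intervention section).** "34 training sessions offered over a 16-week period", beginning at T1. The Abstract puts T3 two months after the program ends.
- **Outcomes (Table 1, Blood biomarkers).** "Bone turnover (serum procollagen type 1 N-terminal peptide, osteocalcin, C-terminal cross-linking telopeptide, and 25-hydroxyvitamin D", measured at all four times. The Outcomes overview presents such measures as showing what the intervention may do. Sample Size Estimation names body composition and bone mineral density as the main outcomes.
- **Analysis (Quantitative and Qualitative Analyses).** Hypothesis 1 is tested by one-way repeated-measures ANOVA or Friedman tests, with T0–T1, T1–T2 and T2–T3 comparisons. No term for supplement use is described.
- **Cointerventions (Potential Challenges).** Only unintended ones are to be documented, and adjustment for them is no more than a possibility.

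**The concern.** A self-controlled design has one safeguard: nothing except the program changes between the control phase and the intervention phase. Here the study itself changes something at T0 in an unknown share of participants, and changes diet instruction in everyone at an unstated time. The control phase is therefore the first four weeks on a new supplement for those participants, not an undisturbed period.

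The problem is sharpest for 25-hydroxyvitamin D. The supplement is given against vitamin D deficiency, so it is meant to move that marker, and the same marker is scored as a response to walking. For bone turnover, bone density and body composition the link is less direct, but two of these are the main outcomes. A one-way model over time pools new and established supplement users, so it cannot tell the two sources of change apart. The safeguard for cointerventions does not reach a supplement and diet advice that the study intends.

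**Working it through.** The protocol gives no figure for the effect of the supplement or the diet advice, so there is no stated number to reproduce on this point. The protocol's dates fix the exposure; the rest is shown over a range of assumptions.

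**Exposure of a participant newly supplied at T0**
- T1: 4 weeks (Study Design).
- T2: 4 + 16 = 20 weeks (Intervention section).
- T3: 20 + about 8 = about 28 weeks (Abstract). One year's supply spans all of this.
- 16 of the first 20 supplemented weeks lie inside T1–T2. This is calendar time, not effect.

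**Assumption A: approach to a plateau.** With half-time h weeks, the share of the eventual change reached by week t is g(t) = 1 − 2^(−t/h). The T0–T1 share is g(4), the T1–T2 share is g(20) − g(4), and the T2–T3 share is g(28) − g(20). No value of h is in the documents.

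| h (weeks) | T0–T1 | T1–T2 | T2–T3 | T1–T2 minus T0–T1 (points) |
|---|---|---|---|---|
| 1 | 94% | 6% | 0% | −88 |
| 2 | 75% | 25% | <1% | −50 |
| 3 | 60% | 39% | 1% | −22 |
| 4 | 50% | 47% | 2% | −3 |
| 8 | 29% | 53% | 9% | +24 |
| 16 | 16% | 42% | 12% | +26 |

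Example for h = 3: g(4) = 1 − 2^(−4/3) = 0.603; g(20) = 1 − 2^(−20/3) = 0.990; the difference is 0.387.

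The sign in the last column changes where g(20) = 2g(4). With x = 2^(−4/h) this is x + x² + x³ + x⁴ = 1, so x ≈ 0.519 and h ≈ 4.2 weeks.

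**Assumption B: linear drift.** T1–T2 carries 16/4 = 4 times the T0–T1 drift. Subtracting the control-phase change removes a quarter of it.

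**What this does to the two comparisons.** In the raw T1–T2 test, any supplement response left after T1 counts as program effect. Against the control phase, as Hypothesis 1 requires, a half-time below about 4 weeks makes the T0–T1 change the larger one. It also enlarges the individual detectable-change criterion, and does so only in new starters.

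**Scale for a main outcome (illustration only).** Sample Size Estimation gives a tibia density target of 532 − 466 = 66 mg/cm³ with SD 70. Treat 70 as the SD of change, take n = 20, a paired t test at two-sided 5%, and no walking effect. If non-walking change in T1–T2 equals the given fraction of 66, the chance of a significant result is:

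| Fraction of 66 | Alpha 5% | Alpha 5%/3 |
|---|---|---|
| 5% | 5.5% | 1.9% |
| 10% | 6.9% | 2.5% |
| 25% | 17% | 7.9% |
| 50% | 52% | 33% |

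Nothing in the documents says which row applies.

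**The case against.** The strongest reply is that starting at T0 rather than T1 works as a four-week run-in. If vitamin D status settles quickly, most of the response is over before walking begins, and comparison with the control phase is then conservative. This stands: a reader might infer that the bias always favours the program, and the table above shows that it does not. The run-in does not rescue the plan, however, because T0–T1 then contains the supplement response and no longer measures natural variability.

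Other points that stand:
- A reader might take the 16 of 20 weeks as the size of the bias. It is exposure time only.
- A reader might conclude that bone and body composition changes cannot be attributed to walking at all. The documents give no supplement or diet effect on either outcome and expect only a few deficient participants. A small drift barely moves the error rate.
- Asking participants not to seek new cointerventions does not contradict a planned background measure supplied by the study.
- Covariate adjustment is often left to a statistical analysis plan, so its absence alone would be no finding. What remains is a conflict among things the article does state: the supplement, the outcome list, the contrasts and the attribution.
- With 20 participants, subgroups will be small. The article itself doubts that analysis by sex is feasible.

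**Conclusion.** The point holds in a limited form. For 25-hydroxyvitamin D the confounding is direct and follows from the protocol's own reason for giving the supplement; a change in this marker is not evidence of a walking effect. The direction of bias is not fixed. It favours the program in the raw T1–T2 test if the supplement moves the marker in the direction counted as benefit. Against the control phase it works for the program if the half-time exceeds about 4.2 weeks, and against it if shorter. These figures rest on an assumed plateau curve.

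For bone density and body composition, confounding is possible and its size is unknown. The number of new starters, their adherence and the timing of the diet advice are not given. The documents do not support a claim that the main results are invalid. They do support a narrower attribution and a cheap change to reporting.

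**What to change.** Leave supplementation and diet advice as they are, and change the analysis and reporting.

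1. Remove 25-hydroxyvitamin D from the Hypothesis 1 efficacy outcomes and report it descriptively as a measure of vitamin D status.
2. Record supplement status at T0 (already taking or newly supplied). Show T0–T1, T1–T2 and T2–T3 changes in bone turnover, bone density and body composition descriptively by that status. Label any supplement-by-time model exploratory at n = 20.
3. Compute or show T0–T1 variability separately for new starters, so that their detectable-change criterion is not read as undisturbed variability.
4. State that T1–T2 changes in these outcomes reflect walking together with the study-supplied supplement and diet advice. Participants already supplemented at T0 can help to separate the supplement, but not the diet advice, which everyone receives.

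The cost is a few sentences of analysis-plan wording and one recorded variable, which must be known anyway to decide who is supplied. The downside is small subgroups and a narrower conclusion.

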## Abbreviations

aBMD: areal bone mineral density
CRIR: Centre de recherche interdisciplinaire en réadaptation du Montréal métropolitain
DXA: dual-energy x-ray absorptiometry
MWESP-Q: Montreal Walking Exoskeleton Satisfaction and Perspectives Questionnaire
pQCT: peripheral quantitative computed tomography
SCI: spinal cord injury
T_0_: control measurement time
T_1_: preintervention measurement time
T_2_: postintervention measurement time
T_3_: retention measurement time
vBMD: volumetric bone mineral density
WU_SCI_: wheelchair users with a chronic spinal cord injury
